## Sample size

No large RCTs have been carried out within the field of aphasia telerehabilitation, especially with the use of videoconference SLT. Previous studies have used interventions not applicable with the current protocol, and have been of varying quality and used small sample sizes. We were, therefore, unable to calculate an a prior accurate sample size. Thus, our pilot RCT will support a more accurate sample size estimate and to inform a definitive trial of the effect of intensive telerehabilitation for aphasia. We will investigate possible effects using the percentile score of the NGA naming subtest where we consider the minimal clinically meaningful effect to be an improvement of 8 percentile scores. Given a standard deviation of 18.17 (based on recently collected data from another project without telerehabilitation), 32 participants will be sufficient to detect a significant improvement within a group between time points using a pairwise comparison, with a significance level of 5 and a power of 80. This will enable the study to make some suggestions on effectivity. Considering possible dropouts, the study aims to include 40 participants in each group, with a total number of 80 subjects. We anticipate that results from this pilot RCT will yield data to inform a more accurate sample size calculation for future definitive RCTs.

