### Objectives and aims

The objective of this pragmatic exploratory pilot RCT is to investigate the feasibility and effectiveness of speech and language training by videoconference given in addition to standard aphasia rehabilitation (usual care).

The primary and main aim of this study is to pilot the RCT of the clinical effectiveness of augmented speech-language therapy intervention for people with aphasia after stroke delivered by videoconference over 4 weeks (in addition to standard aphasia rehabilitation). We will explore whether augmented speech-language therapy by videoconference can improve word naming 4 months post randomization, when compared to standard rehabilitation (usual care).

Secondary aims of our pilot trial are to inform our intervention content, delivery, technology as well as software and training requirements. We will also gather data to enhance our understanding of anticipated recruitment, intervention adherence and dropout and future sample size calculations and our choice of outcomes. We also aim to explore the links between our intervention and naming, functional communication, quality of life and other language impairments than naming at 4 months post randomization, and whether it is sustainable and feasible with regards to ethical, technical, logistic, patient and data safety aspects.

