## Outcome measures

### Primary endpoint

The primary endpoint of this study is naming ability 4 month post randomization, measured by the subtest “naming” in the NGA. The minimum difference of 8 percentile score is considered clinically significant. For the assessment of language functioning, the NGA [27] with the subtests comprehension, naming and repetition is included in the test battery. Percentile scores (i.e., percentile rank compared to the norm material of the NGA) will be used because they – for all severity levels of aphasia – mirror clinically relevant progression more accurately than raw scores.

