## Discussion

This protocol describes a pragmatic, pilot randomized controlled trial (phase II exploratory trial) that should make a valuable contribution to the field of aphasia telerehabilitation.

This trial’s objective is to investigate the feasibility and effectiveness of augmented SLT delivered via videoconference in addition to the standard SLT that the participants are already receiving. To our knowledge, there are no RCTs of this size that have explored the use of videoconferencing in providing an augmented, intensive SLT intervention for aphasia after stroke.

Our trial will look at the feasibility of scaling the intervention up for a larger trial and clinical implementation. Future studies may draw upon our findings if the trial is shown to be feasible, not harmful and indicates effects to be explored beyond this pilot. Our trial might offer some insight into videoconferencing as an effective mode of delivering speech and language interventions in the rehabilitation of people with aphasia, as we have chosen also to investigate clinically meaningful improvement. The trial does not meet sample size based on our assumptions for power calculation; however, large effect sizes might result in significant effects possibly influencing clinical practice. The main purpose of the study, however, is to contribute to the development of future fully powered definitive trials on the effectiveness of this therapy approach, also compared to – and not only in addition to – standard care.

A recent review of the effectiveness of SLT for post-stroke aphasia [8] suggests that intensity may be a key predictor for outcome. This trial investigates the feasibility of telerehabilitation as a supplement to increase the intensity of therapy within aphasia services with limited resources amongst a patient population with common mobility problems and fatigue within a geographically remote context. If telerehabilitation can be used within such a setting, our trial may demonstrate potential for change in future practice. Future studies examining SLT via videoconference as an alternative to usual care will be informed by this study. By shedding light on feasibility aspects through the data gathered using qualitative research methods and logs to map technical errors, we will expect to develop a greater understanding of SLT via videoconference.

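### The sample size rests on a within-group change over time, but the trial asks a between-group question for which no power or precision is stated

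*Protocol article*

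**What the plan says.** All references are to the protocol article.

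- **Sample size, effect:** "we consider the minimal clinically meaningful effect to be an improvement of 8 percentile scores". The Primary endpoint section gives the same threshold: "The minimum difference of 8 percentile score is considered clinically significant".
- **Sample size, calculation:** the SD is 18.17, taken from another project without telerehabilitation. On that basis "32 participants will be sufficient to detect a significant improvement within a group between time points using a pairwise comparison". The stated level is 5% and the stated power 80%. The section then raises the number to 40 per group, 80 in total, to allow for dropout.
- **Sample size, inference:** the sentence that follows the calculation reads "This will enable the study to make some suggestions on effectivity".
- **Question:** Objectives and aims says the trial will explore whether the added therapy "can improve word naming 4 months post randomization, when compared to standard rehabilitation (usual care"). The abstract plans between-group comparisons by intention to treat. The Statistical analysis section plans mixed models that look at differences over time and between groups.
- **Discussion:** "The trial does not meet sample size based on our assumptions for power calculation". It adds that large effects might still reach significance and possibly influence practice, and that the main purpose is to prepare fully powered trials.

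**The concern.** The only power statement in the article concerns a contrast that the trial was not randomised to test. Its 80% applies to change over time inside one arm. The next sentence treats that as a basis for saying something about effectiveness.

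A gain from baseline in one arm cannot carry that inference here:

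- Patients enter at any time after stroke, including the acute phase, so some may recover spontaneously.
- Entry requires a naming percentile of 70 or lower on the same subtest that is the primary endpoint, so some regression to the mean is expected.
- The test is given three times.
- Both arms receive usual speech and language therapy.

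The control arm is there to remove these influences, and the sample size argument does not use it.

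The section also cannot be squared with the Discussion. One reads as though 40 per group satisfies a calculation with a dropout allowance. The other says the requirement is not met, and the calculation that fails is never shown. At stake is which result the trial may cite when it comments on effectiveness, and how precise a reader should expect that result to be.

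**Working it through.** **Inputs from the Sample size section.** Difference δ = 8, SD = 18.17, significance level 5%, power 80%, n = 32 evaluable and 40 recruited per group (32/0.8 = 40, so 20% dropout is implied). The section does not give the sidedness, or say whether 18.17 is the SD of change or of scores at one time point. A paired calculation needs the SD of change, so that reading comes first.

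**Step 1. Reproduce the stated 32.** Normal formula: n = [SD × (z_α + z_power)/δ]².

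- One-sided 5%: [18.17 × (1.6449 + 0.8416)/8]² = 31.9, so 32. This matches.
- Two-sided 5%: [18.17 × (1.9600 + 0.8416)/8]² = 40.5, so 41. This does not match.
- Exact paired t-test: 34 one-sided, 43 two-sided.
- Paired t power at n = 32: 78.5% one-sided, 67.5% two-sided.

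If 18.17 were the SD of scores, a two-sided normal calculation could also give 32. The SD of change would have to be 16.15, which implies a correlation of 1 − 16.15²/(2 × 18.17²) ≈ 0.60. The article states no such correlation.

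**Step 2. The between-group contrast, unadjusted.** SE = 18.17 × √(2/n). Power comes from the noncentral t with 2n − 2 degrees of freedom and noncentrality 8/SE.

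| | 32 per arm | 40 per arm |
|---|---|---|
| SE | 4.54 | 4.06 |
| 8/SE | 1.76 | 1.97 |
| Power, two-sided 5% | 41.1% | 49.4% |
| Power, one-sided 5% | 53.9% | 62.1% |
| 95% CI half-width | 9.1 | 8.1 |
| Difference detectable with 80% power, two-sided | 12.9 | 11.5 |

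With a two-sided test, 80% power at 8 points needs 82 evaluable per arm.

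**Step 3. Allow for baseline adjustment.** The planned mixed model may gain power from the baseline score. The correlation r between baseline and follow-up is not in the article, so it is an assumption. The residual SD is 18.17 × √(1 − r²) if 18.17 is the SD of scores, and 18.17 × √((1 + r)/2) if it is the SD of change. Two-sided 5% t-test, 32 / 40 per arm:

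| Assumed r | 18.17 = SD of scores | 18.17 = SD of change |
|---|---|---|
| 0.3 | 44% / 53% | 58% / 67% |
| 0.5 | 52% / 61% | 52% / 61% |
| 0.7 | 68% / 78% | 47% / 56% |
| 0.8 | 82% / 90% | 45% / 54% |

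At r = 0.5 the two readings coincide (residual SD 15.74). Power passes 80% at both sizes only if 18.17 is the SD of scores and r is about 0.8 or more. If 18.17 is the SD of change, power stays below 80% at both sizes even at r = 0 (69% / 79%).

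**The case against.** The strongest reply is that the article is candid. It calls the trial an exploratory pilot and says that no accurate sample size could be calculated in advance. It labels the 80% as a within-group figure, and it admits in the Discussion that the sample size is not met. The main aim is to pilot the trial, and effectiveness is something it will explore. A pilot does not need 80% power for its randomised contrast, and its absence is not a defect. That stands, and it lowers the severity.

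Three stronger readings are tempting, and the article does not support them:

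- **That the true power is half of what is claimed.** The 80% is not offered as between-group power. Setting a one-sided 80% against a two-sided 41-49% also mixes conventions; on the one-sided basis that reproduces 32, between-group power is 54-62%. The low figures further assume an unadjusted test.
- **That effectiveness will be judged by a pre-post test in one arm.** The abstract and the Statistical analysis section both plan between-group comparisons.
- **That a known share of such trials would give a false positive pre-post result.** Any such rate needs a size for natural recovery, practice and regression to the mean. The article gives none, and it enrols chronic as well as acute patients.

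The reply leaves two things untouched. The sentence in the Sample size section still draws effectiveness from the wrong contrast, and the conflict with the Discussion remains.

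**Conclusion.** The point holds, at moderate severity. The stated calculation addresses change within a group, while the aims and the planned analysis address a difference between groups. The article gives neither power nor precision for that difference.

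From the article's own 8 points and SD of 18.17, an unadjusted two-sided 5% comparison has about 41% to 49% power. The expected 95% CI half-width is about 9 to 8 points, so it is at least as wide as the difference called clinically meaningful. These are not single-valued facts: they move to 54-62% one-sided, and to about 52-61% with baseline adjustment at an assumed correlation of 0.5. Only the combination of a score SD and a correlation near 0.8 lifts power above 80% at both sizes.

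Separately, with 18.17 as the SD of change, the stated 32 implies an undeclared one-sided test. None of this means that the pilot must recruit more patients.

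**What to change.** In the Sample size section:

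1. State whether the test is one- or two-sided, and whether 18.17 is the SD of change or of scores.
2. Replace the paired statement with the between-group power, or preferably the expected CI width, at 32 and 40 per arm under those declared assumptions. If baseline adjustment is claimed, give the assumed correlation and a range.
3. Delete the sentence that ties the paired comparison to effectiveness.
4. Say that within-group changes are descriptive, and that any suggestion of effectiveness rests on the between-group estimate and its confidence interval at 4 months.
5. Align the section with the Discussion, so that the calculation said not to be met is the one shown.

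The cost is wording only. Patient numbers, endpoint, visits and model stay as they are, so the 50 participants already randomised are unaffected. The price is a less favourable headline figure.

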## Statistical analysis

Data will be analyzed on an intention-to-treat basis. Descriptive statistics will be applied and the characteristics of the sample will be described. The trial is a longitudinal study with continuous repeated measurements. The data will be analyzed by using mixed models. A mixed model is preferred to the more traditional repeated measures analysis of variance (ANOVA) because of its advantages in the way in which it accommodates missing values. Data will be examined for differences over time and between groups. Subgroup analysis will be performed to explore factors considered to affect the outcome of the trial like differences in time since onset of stroke or demographic and stroke-related factors. Qualitative data collected from semi-structured interviews will be suitably coded for qualitative responses to be categorized and examined.

## Discussion

This protocol describes a pragmatic, pilot randomized controlled trial (phase II exploratory trial) that should make a valuable contribution to the field of aphasia telerehabilitation.

This trial’s objective is to investigate the feasibility and effectiveness of augmented SLT delivered via videoconference in addition to the standard SLT that the participants are already receiving. To our knowledge, there are no RCTs of this size that have explored the use of videoconferencing in providing an augmented, intensive SLT intervention for aphasia after stroke.

Our trial will look at the feasibility of scaling the intervention up for a larger trial and clinical implementation. Future studies may draw upon our findings if the trial is shown to be feasible, not harmful and indicates effects to be explored beyond this pilot. Our trial might offer some insight into videoconferencing as an effective mode of delivering speech and language interventions in the rehabilitation of people with aphasia, as we have chosen also to investigate clinically meaningful improvement. The trial does not meet sample size based on our assumptions for power calculation; however, large effect sizes might result in significant effects possibly influencing clinical practice. The main purpose of the study, however, is to contribute to the development of future fully powered definitive trials on the effectiveness of this therapy approach, also compared to – and not only in addition to – standard care.

A recent review of the effectiveness of SLT for post-stroke aphasia [8] suggests that intensity may be a key predictor for outcome. This trial investigates the feasibility of telerehabilitation as a supplement to increase the intensity of therapy within aphasia services with limited resources amongst a patient population with common mobility problems and fatigue within a geographically remote context. If telerehabilitation can be used within such a setting, our trial may demonstrate potential for change in future practice. Future studies examining SLT via videoconference as an alternative to usual care will be informed by this study. By shedding light on feasibility aspects through the data gathered using qualitative research methods and logs to map technical errors, we will expect to develop a greater understanding of SLT via videoconference.

When it comes to evaluate the feasibility of telerehabilitation for aphasia, broad participant inclusion criteria in this trial may be regarded as strength. Recent evidence suggests that there may be an interaction between timing post stroke and tolerance of high-intensity SLT [8]. By including participants at all stages of aphasia, from acute to chronic, the data will be more clinically representative for evaluating feasibility features, and of greater ecological validity to the population of people with aphasia. This trial is pragmatic in nature, and due to ecological validity, practicability and ethical issues, we have chosen to examine the effect of additional aphasia telerehabilitation alongside standard SLT in comparison to standard SLT only. As telerehabilitation is relatively new to the field of aphasia research and there is limited pre-existing evidence for the primary and secondary outcomes of our trial, it is considered unethical to prevent the patients from receiving usual care. Thus, an added benefit of this design is to reassure potential participants that randomization may augment their access to therapy and not restrict it.

### Trial status

Recruitment of patients started in May 2016, and 50 participants have been recruited and randomized into the trial.

## Abbreviations

ANOVA: Analysis of variance
CETI: Communicative Effectiveness Index
CILT: Constraint-induced language therapy
CONSORT: Consolidated Standards of Reporting Trials
HRQL: Health-related quality of life
ITT: Intention-to-treat
NGA: Norwegian Basic Aphasia Assessment
NHN: Norwegian Health Net
NUMA: Newcastle University Aphasia Therapy Resources
RCT: Randomized control trial
SAQOL-39: Stroke and Aphasia Quality of Life Scale-39
SLP: Speech-language pathologists
SLT: Speech and language therapy
TIDieR: Template for Intervention Description and Replication
VAST: Verb and Sentence Test
